### Qualitative data

Audio-recorded intervention sessions will be transcribed, and content will be analysed (1) to document the frequency with which various strategies were used by nurses and the perceived effectiveness and satisfaction with the strategies and (2) to identify common themes that reflect issues impacting the intervention, including situational, patient-related, nurse-related or intervention-related factors. This analysis will provide useful information regarding intervention processes whilst also enabling assessment of adherence to the intervention protocol.

### Economic analyses

Intervention resource costs will be aggregated across the groups to assess the incremental cost differences. We will also explore the incremental health benefits of the intervention (each of the arms separately) over and above what occurs with usual care as measured by the EQ-5D scores for suitability within a potential cost-effectiveness analysis. Medicare data on doctor visits and medication use (type, quantity and associated cost) will be analysed to obtain means and 95% confidence intervals using bootstrapping statistics [43] to account for the expected rightward-skewing nature of health-care resource use. Bootstrapped mean differences in health-care utilisation across the three groups will be assessed using Wald tests and calculated using Stata/SE 12 software (StataCorp, College Station, TX, USA).

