**Methods/Design:**

This is a preliminary study in which 120 patients will be recruited. A prospective randomised controlled trial of the H&N Cancer Survivor Self-management Care Plan (HNCP) involving pre- and post-intervention assessments will be used. Consecutive patients who have completed a defined treatment protocol for H&N cancer will be recruited from two large cancer services and randomly allocated to one of three study arms: (1) usual care, (2) information in the form of a written resource or (3) the HNCP delivered by an oncology nurse who has participated in manual-based training and skill development in patient self-management support. The trained nurses will meet patients in a face-to-face interview lasting up to 60 minutes to develop an individualised HNCP, based on principles of chronic disease self-management. Participants will be assessed at baseline, 3 and 6 months. The primary outcome measure is quality of life. The secondary outcome measures include mood, self-efficacy and health-care utilisation. The feasibility of implementing this intervention in routine clinical care will be assessed through semistructured interviews with participating nurses, managers and administrators. Interviews with patients who received the HNCP will explore their perceptions of the HNCP, including factors that assisted them in achieving behavioural change.

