## Methods/Design

### Study aims and hypotheses

Our primary aim in this study is to evaluate the effectiveness of a focused intervention (the HNCP) in improving the QoL of H&N cancer survivors. The HNCP will be developed for each patient in collaboration with an oncology nurse who has participated in focused training in developing an individual’s self-management capacity and will receive clinical supervision during the delivery of the intervention.

Our secondary aims in the study are to evaluate (1) the impact of the HNCP on patient self-efficacy, mood and ability to engage in self-management behaviours that promote optimal health and well-being, (2) the cost impact on the health system of using this model of care in routine clinical practice and (3) the feasibility of integration of the HNCP into routine clinical practice, including identification of systems and patient barriers through interviews with participating nurses, nursing and medical directors of clinics, and patients.

We hypothesise that (1) at 6 months following the intervention, patients who receive the HNCP will have significantly improved QoL compared with patients who do not receive the HNCP, (2) the HNCP will be highly acceptable to patients and (3) at 6 months following the intervention, patients who receive the HNCP will be using significantly fewer health-care resources than patients who do not receive the HNCP.

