#### Patients

The patients eligible for this study must have received treatment for H&N cancer at one of the two cancer services. The inclusion criteria are (1) age 18 years or older; (2) completion of a defined treatment protocol for cancer of the tongue; mouth; salivary glands; pharynx; oro-, hypo- nd/or nasopharynx; nasal cavities; middle ear; sinuses; or larynx or completion of a defined treatment protocol for nonmelanoma skin cancers of the head and neck requiring treatment known to cause toxicity (for example, any one or combination of surgery, radiotherapy or chemotherapy); and (3) possess physical, cognitive and mental status enabling participation in the study. Exclusion criteria are (1) inability to speak and read English; (2) currently receiving low-toxicity treatment for H&N cancer (for example, laser therapy alone); (3) the presence of severe mental, cognitive or physical conditions that would limit the patient’s ability to participate in the study or that require regular ongoing specialist treatment; and (4) advanced disease if life expectancy is expected to be less than 6 months. Informed consent to participate will be obtained from all patients recruited into the study.

There is insufficient evidence from other RCTs on which to base calculation of an adequate sample size for assessing a psychosocial intervention for H&N cancer patients. There are also limited published data about meaningful changes in scores on the Functional Assessment of Cancer Therapy–Head and Neck (FACT–H&N) [32], although this QoL instrument is deemed the most appropriate measurement tool for capturing the unique concerns of patients with H&N cancer [33]. Hence, for this preliminary study, the sample size of 40 patients per group (a total of 120 patients) is based on our capacity to enrol and retain patients, and to conduct the interventions and follow-up, within the time frame for which the study is funded [34]. This study is not powered for hypothesis testing, but it will allow us to determine which changes in the QoL measurement are meaningful to patients and will assist us in calculating the sample size for a subsequent, larger, multisite RCT in which a formal economic cost-effectiveness study can be included.

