### Economic study

The economic study will be undertaken from a health-care provider’s perspective (public and private hospitals) and will involve assessment of (1) intervention resources by identifying, quantifying and valuing resources using standard methods [42] and (2) utilisation and cost of doctor visits and medications for all participants over the course of a 12-month period covering 3 months preintervention, 6 months during the intervention and 3 months postintervention completion.

Investigators will maintain detailed records of direct costs of delivering the intervention (staffing, training, telephone costs, office consumables and printing and production of educational materials) for the duration of the study. Resources will be valued using standardised national fee schedules, salary schedules for personnel and retail prices for other general consumables. To test the occurrence of the medical offset effect as a benefit of the intervention, administrative data on doctor visits and medications will be requested from Medicare Australia records.

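### Health-care utilisation is compared without a named covariate although each patient's prior use is collected; adjusting for it would be a cheap gain in precision, not the repair of an error

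*Protocol article*

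**What the plan says.** The abstract lists utilisation among the secondary outcomes: "The secondary outcome measures include mood, self-efficacy and health-care utilisation". Under Study aims and hypotheses, hypothesis 3 predicts that, 6 months after the intervention, "patients who receive the HNCP will be using significantly fewer health-care resources than patients who do not receive the HNCP".

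The Economic study section defines the data as visits and medications for all participants over a "12-month period covering 3 months preintervention, 6 months during the intervention and 3 months postintervention completion". The source is administrative: "administrative data on doctor visits and medications will be requested from Medicare Australia records".

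The Economic analyses section gives this outcome its own method. Means and 95% confidence intervals are bootstrapped "to account for the expected rightward-skewing nature of health-care resource use", and then "Bootstrapped mean differences in health-care utilisation across the three groups will be assessed using Wald tests", in Stata. The section mentions no covariate, no site term and no role for the 3 pre-intervention months, and it does not say which months of the 12 are contrasted.

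The Statistical analyses section describes something different: an SPSS mixed model for change in mean scores across baseline, 3 and 6 months, with control for site and a group-by-time term.

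**The concern.** The best single predictor of a patient's later service use that the trial will hold is probably the same patient's earlier use. It is already being requested for everyone, yet the stated between-group estimator does not use it. The bootstrap deals with skewness and does nothing about differences between arms in prior use.

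Allocation is by a computer-generated random list, and the article mentions no balancing on prior use. With 40 patients per arm, moderate imbalance between arms will be common. The cost-offset question rests on this comparison, and the Discussion says that no firm evidence for such an effect exists yet. The estimates are also meant to help plan a larger trial with a formal cost-effectiveness study. A tighter interval, less dependent on which patients happened to fall in which arm, would serve both purposes.

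**Working it through.** **Inputs from the article.** Three arms of 40: "the sample size of 40 patients per group (a total of 120 patients) is based on our capacity to enrol and retain patients". The total reproduces as 3 × 40 = 120. No effect size, standard deviation, dropout rate or power is given, so there is no power figure to reproduce.

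**Assumed.** rho, the correlation between pre-period and later utilisation, from 0 to 0.7; two-sided 5% level; a 0.5 SD difference for the illustrative power.

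**Chance imbalance in prior use.** The standard error of a difference between two arm means is √(2/40) = 0.224 SD.
- P(difference above 0.25 SD) = 2 × (1 − Φ(0.25/0.224)) = 0.26 for a given pair of arms.
- P(difference above 0.5 SD) = 2 × (1 − Φ(0.5/0.224)) = 0.025 for a given pair.
- By simulation, the probabilities that at least one of the three pairs exceeds these limits are about 0.50 and 0.065.

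**Effect of adjustment.** Regression on prior use multiplies the variance of the arm difference by 1 − rho². The equivalent sample size per arm is 40/(1 − rho²). A 0.25 SD imbalance in prior use shifts the unadjusted difference by rho × 0.25 SD. A simple change score has variance ratio 2 − 2rho, assuming equal variance before and after.

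| rho | variance ratio, adjusted | SE reduction | equivalent n per arm | power at 0.5 SD | shift from 0.25 SD imbalance | variance ratio, change score |
|---|---|---|---|---|---|---|
| 0 | 1.00 | 0% | 40 | 61% | 0 | 2.0 |
| 0.2 | 0.96 | 2.0% | 41.7 | 63% | 0.05 SD | 1.6 |
| 0.3 | 0.91 | 4.6% | 44.0 | 65% | 0.075 SD | 1.4 |
| 0.5 | 0.75 | 13.4% | 53.3 | 73% | 0.125 SD | 1.0 |
| 0.7 | 0.51 | 28.6% | 78.4 | 88% | 0.175 SD | 0.6 |

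The change score is worse than no adjustment below rho = 0.5 and worse than regression adjustment at every value in the table.

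**Check under skewness.** In 8,000 simulated trials of 40 against 40 with log-normal use (log SD 1), linear adjustment gave variance ratios of 1.01, 0.96, 0.82 and 0.58 at raw-scale correlations of 0, 0.20, 0.38 and 0.59. The gain survives a skewed outcome. With no correlation there is a loss of about 1%.

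**The case against.** **The comparison is not wrong.** A reader might infer that the planned contrast is biased, or that a few heavy users could create or hide a cost offset. The documents do not support that. An unadjusted difference between randomised arms is unbiased, and its interval already allows for chance imbalance. Even at rho = 0.5, a 0.25 SD imbalance shifts the difference by 0.125 SD, which is 0.125/0.224 = 0.56 of a standard error.

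**Lack of adjustment is inferred.** The article never calls the differences raw or unadjusted. A bootstrapped difference with a Wald test could come from a regression, and a fuller document may name covariates. One might also argue that the mixed model covers utilisation, since that is a secondary outcome. The first part stands as a caution. The second is the weaker reading: that model is for scores at three assessments, whereas Medicare use accumulates over periods and has its own estimator, test and software.

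**The gain may be small.** The HNCP is delivered within 1 month of completing treatment, so the preceding 3 months largely cover active treatment. Use in that period may reflect the treatment protocol more than personal habit. The exclusion of patients with severe conditions needing regular specialist care may also remove some habitual heavy users. Both make a low rho plausible, so it would be wrong to describe the extra precision as guaranteed or free.

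**Power is a poor yardstick here.** The Patients section says that the study is not powered for hypothesis testing. That stands, and the power column above is only illustrative. The article nevertheless plans Wald tests and intends its estimates to inform a larger trial, so precision keeps its value.

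**Conclusion.** The point holds as an improvement to a stated estimator. The article collects pre-intervention utilisation for all participants and names, for that outcome alone, a between-group method without a covariate. Using the baseline value would improve precision and reduce sensitivity to chance imbalance in prior use.

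The expected gain is modest if the pre-period mainly reflects cancer treatment and substantial only if rho reaches about 0.5 or more. All these figures rest on an assumed rho and on a roughly linear relation between earlier and later use. The outcome is secondary and the study preliminary, so the priority is low to moderate.

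**What to change.** In the Economic analyses section, replace the mean difference with a regression-adjusted one:
- Regress each patient's post-allocation utilisation, and separately cost, on arm, utilisation (or cost) of the same type in the 3 months before allocation, and site.
- Bootstrap the adjusted arm differences by resampling patients within arm, and apply the Wald tests to these.
- State which months form the outcome. Count the covariate back from allocation, so that it is defined alike in all three arms and cannot be affected by arm.
- Keep the unadjusted bootstrapped means per arm as description.
- Do not substitute a simple change score.

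The cost is a sentence or two of text and a few lines of Stata, since the records are already requested. The downside is one or two extra parameters, a loss of about 1% in variance if prior use turns out to be uninformative, and a simple rule for patients without a pre-period record. These should be few, because both periods come from the same request. The Trial status section reports eight patients recruited, so the change could be fixed before outcomes are known.

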## Discussion

Despite increasing acknowledgement of the needs of cancer survivors, many cancer services still do not offer focused interventions to promote their well-being. Currently, there is a paucity of research demonstrating effective models of survivorship care that are feasible to deliver in busy clinical services, which are often resource-poor.

This study is the first of its kind in Australia. It targets a patient population that faces the additive challenges of intensive treatments and severe side effects, often against a background of premorbid vulnerability. Despite documented high levels of depression, the lack of a political voice and advocacy has seen the needs of this cancer population neglected relative to those of patients with other cancers, such as breast cancer or, increasingly, prostate cancer.

Embedding the intervention into clinical care is likely not only to be acceptable to patients [44] but also to address the barriers of stigma and the burden of travel to receive assistance [45-47], because the intervention can be delivered to patients in rural and remote areas by appropriately trained local nurses. Furthermore, it has been proposed that supportive care interventions for people with cancer will produce downstream economic benefits in the form of reduced use of physicians’ services and medications due to the intervention’s successfully meeting the specific needs of patients [48]. However, as yet, there is no firm evidence to support this medical “cost-offset effect”.

If successful, this study will (1) provide evidence about a model of care structured to improve QoL in a cancer patient population with unique and complex needs, (2) add to the evidence base with respect to chronic disease self-management interventions and (3) provide a basis for a larger multisite study designed to examine the feasibility and cost-effectiveness of this comprehensive survivorship intervention in different treatment settings.

## Trial status

Fifteen oncology nurses have been recruited and completed training in order to be able to deliver the intervention. Eight patients have been recruited across both sites to date.

## Abbreviations

ACET: Ambulatory care and enhancement team; ACTRN: Australian Clinical Trial Registry number; ENHANCES: Enhancing Head and Neck Cancer Patients’ Experiences of Survivorship; EQ-5D: European Quality of Life Questionnaire (EuroQol) 5-level version; FACT–H&N: Functional Assessment of Cancer Therapy–Head and Neck; H&N: Head and neck; HNCP: Head and Neck Cancer Survivor Self-management Care Plan; HPV: Human papillomavirus; QoL: Quality of life RBWH, Royal Brisbane and Women’s Hospital; RCT: Randomised control trial.
